### 7.2.2 Physical examination

The physical examination includes the following: height, weight, waist circumference, hip circumference, general appearance, superficial lymph nodes, skin and sclera inspection, skull, eyes, ENT, neck, chest, respiratory, cardiovascular, abdomen, musculoskeletal/extremities, and nervous system (must perform the following examinations using the neurology screening kit: a. ankle reflex; b. tactile test with a 10g nylon thread; c. pallesthesia sensibility via tuning fork; d. needle algnesia test; e. thermesthesia sensibility). Baseline data were collected at Visit1. Physical examination items that were found to have changed during subsequent follow-up should be recorded for comparison with baseline.

### **7.2.3 Pulse and blood pressure**

Pulse and blood pressure (BP) should be measured when the patient is quiet and in a sitting position (the patient should have rested comfortably for at least five minutes) and with their right arm outstretched at the same level as the middle part of the sternum. Measurement should be taken under standardized conditions, approximately at the same time of each day, and on the same arm. BP should be measured with the same device and the values be recorded in the original files and in the CRF (the sphygmomanometer should be calibrated regularly according to the manufacturers' instructions). Both systolic blood pressure (SBP), diastolic blood pressure (DBP), and pulse rate should be recorded. Patients with complications of microangiopathy and neuropathy should be tested for autonomic neuropathy, for instance, measurement of postural BP. Postural BP measurement: The patient should lie in supine position for at least 5 minutes before his/her supine BP and pulse could be measured. The cuff should be fastened around his/her right upper arm (be careful not to unite the cuff). Next, the patient should remain standing quietly for 1 minute and then have his/her orthostatic BP and pulse measured (with the same method as measuring a seated BP, where the patient's right arm is outstretched and the cuff is at the same level as the left atrium). The patient should remain standing for 3 more minutes and have his/her BP and pulse measured again. Hypotension could happen immediately or tardively after standing. The condition, where the orthostatic SBP is 20 mmHg lower or DBP is 10 mmHg lower than the supine SBP and DBP respectively, is called postural hypotension.

### **7.2.4 Body temperature (when suspecting fever)**

Body temperature should be measured using a thermometer in degrees Celsius when the patient is quiet, and axillary temperature should be recorded in the CRF. Once the temperature is higher than 38.5 centigrade, the patients should withhold the visit until his or her temperature returned to the normal range (record as an adverse event).

### **7.2.5 ECG**

The 12-lead ECGs should be performed after at least 10 minutes in supine position. The electrodes are to be positioned at the same place for each ECG recording throughout the study. The investigator has to review the ECG and document his interpretation, including

signature and date on the ECG print-out. The original trace and its copies were saved as source data and recorded in the e-CRF according to the investigator's evaluation.

### **7.2.6 BUS of urinary system**

B-Ultrasound examination of the urinary system often includes bilateral kidneys, ureters, bladder (the prostate, for male). Before the examination, the doctor must apply a facial cleanser like coupling agent to the detector, so that the detector could have better contact with skin and the ultrasonic wave could detect into the body. The coupling agent is safe, non-toxic, non-irritating to the skin and could be cleaned with soft paper after the examination. It does not require fasting situation or taking oral intestinal cleaning agent, but the patients are required to drink 300~500 ml water and preferably not urinate within 2~3 hours.

## **7.3 Other assessments**

- GADA: tested in a central laboratory by using radioimmunoassay. The sensitivity and specificity were 82% and 98%, respectively. The assay was sponsored by the Immunology of Diabetes Society (IDS) and has been validated by Islet Autoantibody Standardization Program (IASP) in 2012. Changes of GADA titers will be measured once a year during intervention: at V14 (week 52), and V26 (week 104).
- Genetic testing: tested in a central laboratory. HLA-DQA1, -DQB1, HLA-DRB1, and VDR genotypes will be determined by DNA analysis using polymerase chain reaction (PCR) to amplify exon of DQA1, DQB1, DRB1, and VDR genes followed by standard DNA sequencing-based typing. DNA samples were collected before and after the intervention, and high-throughput sequencing was used to detect changes in immune diversity before and after treatment. Detection is performed on V1, V3, V5, V8, V14, V20 and V26.

- Complications: The complications will be examined according to the conditions of each hospital, which includes: ① macroangiopathy: 1) Color Doppler Ultrasound of carotid artery, vertebral artery, and lower extremities arteries, 2) ECG; ② microangiopathy: 1) retinopathy: fundus examination and photography, 2) diabetic nephropathy: a. UACR, b. calculate eGFR; ③ peripheral neuropathy: 1) electroneuromyography, 2) physical examination using the tools in the neurology screening kit; ④ osteoporosis: bone mineral density. (We will accept Color Doppler Ultrasound of artery, fundus examination and photography, and electroneuromyography results from Grade A Tertiary Hospitals within 6 months prior to screening, and will accept bone mineral density test results from Grade A Tertiary Hospitals within 12 months before the date of randomization).
- a) Urinary albumin-to-creatinine ration (UACR): collect 10-15ml of the participant's urine in clean, regular urine collection tube (or small bottle), and correctly label the basic information of the participant. The specimens do not require further process but to be sealed and tested at each hospital. Attention: do not get vaginal secretion or faeces mixed into the urine sample; patients with hematuria caused by urinary infection or other causes should be re-tested after the hematuria is controlled.
- b) Calculate the estimated glomerular filtration rate (eGFR): use the CKD-EPI formula, or use the "National Kidney Foundation Calculators" to calculate (GFR caculator website: [https://www.kidney.org/professionals/KDOQI/gfr\\_calculator](https://www.kidney.org/professionals/KDOQI/gfr_calculator)).

## 7.4 Collection and processing of biological samples

Refer to Appendix 3: 《*Samples collection, transport and test results report procedures*》

## 8. SAFETY REPORTING AND MEDICAL MANAGEMENT

The Principal Investigator is responsible for ensuring that all staff involved in the research are familiar with the content of the study.

## **8.1 Definition of adverse events (AE) and treatment plans**

Adverse Event refers to an adverse medical event that occurs after a patient or a participant receives treatment, but does not necessarily have a causal relationship with the treatment. Once an adverse event occurs, detailed records, judgements on severity, timely diagnosis and effective treatments and follow-up of the subjects are required.

### **8.1.1 Recording of adverse events**

Regardless of seriousness or relationship to the investigational drug, all AEs should be recorded on the corresponding page(s) in the CRF from the time the subject signed the informed consent form until the end of the study as defined by the protocol for that patient. Any laboratory tests, vital signs or other abnormalities that are medically relevant and clinically meaningful (causing any type of intervention) should be recorded as an adverse event. Including symptomatic; and/or requiring either corrective treatment or consultation; and/or leading to discontinuation or modification of dosing; and/or fulfilling a seriousness criterion; and/or defined as an AE with pre-specified monitoring with immediate notification.

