### **8.1.2 Intensity of adverse events and management**

When filling out the adverse event table, the investigator will use mild, moderate, and severe to describe the intensity of adverse events. To harmonize standards, the intensity of events is ranked as follows.

- (1) Mild: The event does not interfere with the normal daily activity of the subject, and there is no need for symptomatic treatment and discontinuation of dosing.
- (2) Moderate: The event partly affects the subject's normal daily activity and requires symptomatic treatment or discontinuation of dosing.
- (3) Severe: The event obviously interferes with subject's normal daily activity and requires emergency treatment or immediate discontinuation of dosing.

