## 8.6 Treat on hypercalcemia

Clinical manifestations of hypercalcemia are associated with the magnitude and speed of the increase of serum calcium. Mild hypercalcemia may be asymptomatic. symptoms include anorexia, nausea, vomiting, constipation, fatigue, muscle fatigue, reduce of muscle tension, polydipsia, polyuria; drowsiness, confusion, and even coma. ECG may show shortening of Q-T interval, the change of ST-T, atrioventricular block and hypokalemic u waves. If not treated timely, it may result in fatal arrhythmia. Long duration of hypercalcemia can lead to calcium deposition within various tissue and organ, such as the conjunctiva, periarticular and kidney stones. It should be noted that serum albumin have impact on calcium concentration. Elevated serum calcium levels can be categorized into mild, moderate and severe.

- Mild hypercalcemia: total serum calcium values above the upper reference limit, but  $< 3\text{mmol/L}$ ;
- Moderate hypercalcemia: total serum calcium values  $3\text{-}3.5\text{mmol/L}$ ;
- Severe hypercalcemia: total serum calcium  $> 3.5\text{mmol/L}$ , while causing a series of serious clinical manifestations, namely hypercalcemia crisis.

The most common causes of hypercalcemia are primary hyperparathyroidism and malignant tumors, other reasons include: drugs: such as vitamin D, vitamin A, thiazide diuretics, lithium, theophylline, estrogen and anti-estrogen hormones; endocrine diseases, sarcoidosis and other granulomatous diseases, long-term immobilization, familial hypocalcinuric hypercalcemia and milk alkali syndrome. Once the patient's serum calcium is high:

- Confirm the existence of hypercalcemia, measure of serum calcium should be repeated to rule out laboratory error and prolonged tourniquet lashing or other human factors; be aware whether the patient is dehydrated or rise of plasma protein concentration.

- Once hypercalcemia is confirmed, the cause should be identified: researchers can determine whether to simultaneously monitor PTH, 25(OH)D, renal function, urinary calcium/creatinine clearance rate and alkaline phosphatase based on the patient's condition, and seek for other possible causes; if the patient is in the vitamin D3 treatment group, vitamin D3 therapy should be suspended.

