- Treatment of hypercalcemia depends on calcium levels and clinical symptoms. In aspect of mild hypercalcemia, generally no active measures are taken to control blood calcium in patients without clinical symptoms; for symptomatic moderate and severe hypercalcemia patients, immediate treatment may be required according to the cause; when calcium > 3.5 mmol/L, regardless of the presence or absence of clinical symptoms, immediate and effective measures are required: dilatation, promote urinary calcium excretion, inhibit bone absorption, glucocorticoids, and even dialysis to lower blood calcium [26].

When the cause and manifestation of hypercalcemia meet the standards of serious adverse events, it should be reported as a serious adverse event.

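### A confirmed, symptom-free, slightly raised calcium always meets an adverse-event trigger in the vitamin D3 group, but recording the same value in the other two groups is left to an unblinded investigator

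*Protocol*

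**What the plan says.** Protocol 8.1.1 sets the recording rule: laboratory "abnormalities that are medically relevant and clinically meaningful (causing any type of intervention) should be recorded as an adverse event". It then lists the qualifying circumstances: "Including symptomatic; and/or requiring either corrective treatment or consultation; and/or leading to discontinuation or modification of dosing". Two more complete the list: the event is serious, or it is one singled out in advance for special monitoring and prompt reporting.

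Protocol 8.6 classes total calcium above the upper reference limit and below 3 mmol/L as mild. For any suspected case, in any arm, it asks for a repeat measurement and, once confirmed, a search for the cause. At that same step, with no grade threshold, it adds: "if the patient is in the vitamin D3 treatment group, vitamin D3 therapy should be suspended". On treatment it says: "In aspect of mild hypercalcemia, generally no active measures are taken to control blood calcium in patients without clinical symptoms".

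The synopsis and section 2.3 single out potential hypercalcaemia among the safety outcomes. Section 9.4.3 plans a by-group summary of the incidence of adverse events and of abnormal central laboratory results, and a by-group summary of changes in laboratory parameters. Under 7.2.1, the only safety test sent to the central laboratory is 25(OH)D; electrolytes, calcium among them, are measured at each site.

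**The concern.** Whether a calcium value becomes an adverse event depends partly on an action that the protocol orders in one arm only. If asymptomatic mild hypercalcaemia were equally common in all three groups, the adverse-event table could still show an excess under vitamin D3. Section 1.3 (benefit/risk) asks whether safety differs among the three groups and whether any difference relates to vitamin D levels. An outcome ascertained differently by arm cannot answer that cleanly. The trial is open-label, so the discretion left in the other arms is exercised with the allocation known.

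**Working it through.** The point rests on reading the rules together. No figure in the protocol needs to be reproduced.

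**Step 1: one case, two settings.** Take a subject with repeat-confirmed calcium just above the reference limit and no symptoms.

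| Trigger in 8.1.1 | Vitamin D3 group | Other two groups |
|---|---|---|
| Symptoms | No | No |
| Corrective treatment | Generally none (8.6) | Generally none (8.6) |
| Consultation | Possible, through the search for a cause | Possible, through the same search |
| Discontinuation or modification of dosing | Always: suspension is ordered | None ordered; a supplement change is possible (5.6 allows supplements) |
| Seriousness criterion | No | No |
| Pre-specified monitoring with immediate notification | Not assigned to hypercalcaemia in the text | Not assigned to hypercalcaemia in the text |

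Suspending a drug is at least a modification of dosing, so the fourth row does not depend on treating suspension as discontinuation. The vitamin D3 case meets a trigger with certainty; the same case elsewhere meets one only if the investigator judges so.

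**Step 2: does another summary repair this?** The abnormal-result tally in 9.4.3 is for central laboratory results, and calcium is a site test (7.2.1), so it is not covered. The summary of changes from baseline is neutral between arms but does not count patients above the limit. The adverse-event count is left as the only stated incidence measure.

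**Step 3: how large could the effect be?** The documents give neither input needed, so both are assumptions:
- p: true incidence of asymptomatic mild hypercalcaemia, taken equal in every arm;
- q: share of those cases recorded in each group without vitamin D3 (all are recorded in the vitamin D3 group).

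With 100 per group (section 9.2), the expected counts are 100p under vitamin D3 and 100pq in each other group. The expected spurious excess is 100p(1 − q). At p = 0.05 and q = 0.5 this is 5 − 2.5 = 2.5 cases.

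As a yardstick, the last column gives the chance that Fisher's exact test of the vitamin D3 group against one other group yields p < 0.05 with vitamin D3 higher. It sums binomial probabilities over all pairs of counts.

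| p | q | Expected, vitamin D3 | Expected, each other group | Chance of spurious excess |
|---|---|---|---|---|
| 2% | 0 | 2 | 0 | 1.5% |
| 2% | 0.5 | 2 | 1 | 0.6% |
| 2% | 1 | 2 | 2 | 0.2% |
| 5% | 0 | 5 | 0 | 38% |
| 5% | 0.5 | 5 | 2.5 | 6.7% |
| 5% | 1 | 5 | 5 | 1.0% |
| 10% | 0 | 10 | 0 | 94% |
| 10% | 0.5 | 10 | 5 | 19% |
| 10% | 1 | 10 | 10 | 1.4% |

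The rows with q = 1 show what equal recording gives.

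**Step 4: grading gaps.** Under 8.1.2, a mild event is one where "there is no need for symptomatic treatment and discontinuation of dosing". A moderate event must also partly affect daily activity. If suspension is read as discontinuation, a symptom-free case with vitamin D3 suspended fits neither grade. Separately, 8.6 defines severe hypercalcaemia as above 3.5 mmol/L "while causing a series of serious clinical manifestations, namely hypercalcemia crisis", yet says that above 3.5 mmol/L, "regardless of the presence or absence of clinical symptoms, immediate and effective measures are required". A symptom-free value above 3.5 mmol/L has no clear grade.

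**The case against.** The strongest reply is that the protocol does not stop such a case from being recorded in the groups without vitamin D3. The triggers in 8.1.1 are alternatives, and consultation is one of them. The repeat test and search for a cause in 8.6 apply to every arm. Section 1.3 tells physicians to look for causes of hypercalcaemia and treat accordingly. Section 7.2.1 says that any laboratory abnormality might qualify, and 8.1.3 names hypercalcaemia among particular adverse events without limiting it to one arm. The statement about active measures is qualified as general and concerns only measures to control blood calcium. All of this stands. A reader might infer that the same value counts under vitamin D3 and never elsewhere, so that bias is certain. The text supports only certain recording in one arm and discretionary recording in the other two.

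A reader might also put a significance level on a few vitamin D3 cases against none in the other groups combined. That would need zero recording elsewhere, an incidence the protocol does not give, and a pooled comparison it does not plan. Section 4.1 excludes patients with hypercalcaemia at entry, and the synopsis and 9.4.3 describe summaries rather than tests for safety endpoints.

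It can be said that tables of values above the limit belong in the analysis plan. That is fair for layout. The recording rule and the restriction of the tally to central results, however, are fixed in the protocol itself. The summary of laboratory changes softens the problem without replacing a count.

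The intensity point is a gap in wording; it does not show that vitamin D3 cases would be graded upward. The gap above 3.5 mmol/L adds nothing to the between-arm argument.

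**Conclusion.** The point holds in this limited form: ascertainment of a named safety outcome can differ by arm, and if it does, the direction is against vitamin D3. This assumes that the suspension order is followed and that some cases in the other groups go unrecorded. The size cannot be derived from the documents. In the illustration it is small at 2% incidence (at most a 1.5% chance of a spurious excess). It becomes material only if incidence is several per cent and recording elsewhere is poor: 6.7% to 38% at 5% incidence when half or none of the other groups' cases are recorded. This is a cheap improvement that should be made, and it does not threaten the efficacy conclusions. The grading gaps are separate and minor.

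**What to change.** In 8.1.1 and 9.4.3, define the hypercalcaemia safety outcome identically in all three groups: repeat-confirmed serum calcium above the site's upper reference limit, counted whatever action is taken. Report its incidence by group beside the adverse-event table. Albumin-adjusted calcium can be tabulated as well, since 8.6 notes that albumin affects calcium and Table 1 schedules albumin at the same visits as electrolytes.

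Separately, reconcile 8.1.2 with 8.6, and the two statements in 8.6 with each other, so that a symptom-free case with vitamin D3 suspended and a symptom-free value above 3.5 mmol/L each have a grade. Management rules stay as they are.

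The cost is a few sentences and one derived variable, with no new scheduled tests. The downside is a few more laboratory events listed in the two groups without vitamin D3.

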### **8.1.2 Intensity of adverse events and management**

When filling out the adverse event table, the investigator will use mild, moderate, and severe to describe the intensity of adverse events. To harmonize standards, the intensity of events is ranked as follows.

- (1) Mild: The event does not interfere with the normal daily activity of the subject, and there is no need for symptomatic treatment and discontinuation of dosing.
- (2) Moderate: The event partly affects the subject's normal daily activity and requires symptomatic treatment or discontinuation of dosing.
- (3) Severe: The event obviously interferes with subject's normal daily activity and requires emergency treatment or immediate discontinuation of dosing.

### **8.1.3 Treatment of adverse events**

Investigators should determine whether to suspend the clinical trial according to the severity of the event and provide the diagnosis and necessary treatment based on his/her clinical experience. All adverse events should be tracked for investigation, the process and the result of the treatment should be recorded in details until the situation is properly solved or the patient's condition is stable, abnormal test results must be followed until the figures are normal.

The relevant treatment on some particular adverse events, such as severe nausea and vomiting, hypoglycemia, hypercalcemia and vitamin D intoxication should refer to 8.4-8.7.

### **8.1.4 Follow-up of adverse events**

Any AEs are unresolved or recovered at the last visit/study discontinuation or subject withdrawal from study, the subjects are followed up by the investigator for as long as AEs are relieved/ recovered to baseline/no longer worsening or stable/interpretable by investigator (for the worsening of diseases unrelated to the investigational drug, and without relieved/recovered condition since 30 days from the end of visit)/lost to follow-up.

## **8.2 Definition of serious adverse events (SAEs)**

Serious adverse events: in the course of clinical trials, meeting the necessity of hospitalization or prolongation of hospitalization, disability, incapacity of work, life-threatening or death, congenital abnormality and so on, listed as followings:

- 1) Leading to death
- 2) life-threatening
- 3) Requires in-patient hospitalization or prolongation of existing hospitalization
- 4) lead to persistent or significant disability/incapacity or substantial disruption of the ability to conduct normal life functions

- 5) Cause congenital abnormality or birth defects, etc.
- 6) Important medical events (defined as a medical event that may not be immediately life-threatening or result in death or hospitalization but based upon appropriate medical and scientific judgment, that may jeopardize the subject or may require medical intervention to prevent various serious outcomes listed in the definition above).

The following hospitalization does not regard as SAEs, for there is no “adverse event” associated with hospitalization (eg, there’s no adverse medical event):

- 1) Hospitalization for convenience of fulfilling the examination on complications referred in the study protocol;
- 2) Hospitalization for convenience of routine physical examination;
- 3) Hospitalized for temporal medical care.
- 4) Plan to hospitalize before sign Informed Consent (after taking investigational drug, there’s no change for the plan to hospitalize).

It is important to distinguish between serious and severe AEs. An AE of severe intensity does not necessarily need to be defined as a serious adverse event. For example, nausea that persists for several hours may be considered severe nausea, but not a SAE. On the other hand, a stroke that results in only a limited degree of disability may be considered a mild stroke but still would be a SAE.

